#### *Specific Aim 2: estimate the dose effect on smoking abstinence at six and twelve months for the AR + IVR compared to usual care*

Variation in outpatient service use is used to assess a dose–response effect for cessation services. We test the hypothesis in two ways using the model developed for Specific Aim 1. First, we will include only AR + IVR recipients and redefine X as a multilevel ordinal variable representing intervention dose (D_r_) ranging from no postdischarge intervention to full intervention. The number of levels to D_r_ will be determined using a rank scoring algorithm that includes cessation service program enrollment and completion, cessation medications, and number of IVR follow-up calls received. Additional inputs will be considered based on actual study data. Second, we will rerun the analysis including control group participants with a dose score using the same method. For each analysis, we will conduct trend tests and assess the presence of a dose threshold.

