#### *Power*

A 2:1 ratio of AR + IVR to UC for 900 randomized participants will provide adequate power to detect an eight percentage point difference in thirty-day point prevalence abstinence at six months (our primary outcome), assuming an unbiased method of assigning an outcome to nonrespondents. The unbalanced design requires 864 participants to achieve 80% power, with two-tailed α set at .05, to detect a difference in thirty-day abstinence of eight percentage points between treatment groups. We expect the UC group will achieve a 15% abstinence rate, based on analyses of EMR data (unpublished) for similar populations at each site. An odds ratio of 1.65 for patients with >30 days of follow-up [3] results in a 23% expected abstinence rate for the AR + IVR group. The power calculations were conservative [25-28] and no continuity correction was applied. Rounding up to 900 total participants added an additional measure of conservatism.

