#### *Intervention dose*

We collect inpatient and outpatient smoking cessation counseling and medications provided and used by study participants from the initial inpatient consult through 12-month follow-up. Measures collected are used to assess treatment fidelity and to assess an intervention dose response on the primary outcome. Inpatient treatment measures include: TTS counseling time and content checks; medication dispenses; quit materials provided; and inpatient referrals to outpatient services (counseling programs and medication orders). These data are collected from TTS and EMR data sources. Outpatient treatment measures include: counseling program enrollment and participation, such as telephone quitlines, in-person individual and group programs, and web-based programs; FDA-approved prescription and over-the-counter medications such as buproprion, varenecline, and nicotine patches, gum, lozenges, and sprays. Medications provided and used, including combination therapy, will be assessed from EMR records and participant self-report.

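### The Aim 2 dose score uses post-discharge service use that staying abstinent or relapsing may itself drive, with no cut-off stated for the six-month outcome, so its trend could be spurious in either direction

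*Protocol article*

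**What the plan says.** Specific Aim 2 reuses the Aim 1 regression model but changes the exposure: "First, we will include only AR + IVR recipients and redefine X as a multilevel ordinal variable representing intervention dose". The score draws on joining and finishing cessation programs, on medications, and on how many IVR calls were received. Its inputs are not closed: "Additional inputs will be considered based on actual study data". Trend tests and a search for a dose threshold follow. The analysis is then repeated with usual care (UC) participants scored by the same method.

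The *Intervention dose* section says counseling and medications are recorded as "provided and used by study participants from the initial inpatient consult through 12-month follow-up". It adds: "Measures collected are used to assess treatment fidelity and to assess an intervention dose response on the primary outcome". The primary outcome is 30-day abstinence at six months after randomization. Neither section says which part of the 12-month record enters the six-month score.

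IVR calls are scheduled for days 4, 14, 28 and 49 after discharge and go to the AR + IVR arm only. The *Randomization* section gives the dose analysis as the first of two reasons for 2:1 allocation. The other is the health systems' interest in extending the potential benefit to more participants.

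**The concern.** Taking a call at day 28, finishing a program or completing a course of medication happens while patients are relapsing. A patient who has gone back to smoking may stop answering and drop out, so a low dose is partly a result of failure. Equally, such a patient may seek more help, so a high dose is partly a result of failure. Either way the regression of abstinence on dose mixes any effect of service use with the effect of smoking status on service use.

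Three features add to this:

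- If counseling and medication use after month six is counted, part of the dose comes after the outcome it is meant to explain.
- A score that is still open when data are available, combined with a threshold search, leaves room for choices that favor a trend.
- UC participants cannot receive IVR calls, so in the pooled analysis the score partly re-codes the arm.

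A positive trend would be read as showing that more service produces more quitting, and a flat or negative one as showing that it does not. Neither reading would be safe.

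**Working it through.** **1. The plan's own figure.** Inputs from *Power*: "We expect the UC group will achieve a 15% abstinence rate"; an odds ratio of 1.65 "results in a 23% expected abstinence rate for the AR + IVR group"; "with two-tailed α set at .05"; 2:1 allocation; no continuity correction. With r = 2 and weighted mean p̄ = (0.15 + 2 × 0.23)/3 = 0.2033:

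n(UC) = [1.960 √(p̄(1 − p̄)(1 + 1/r)) + 0.842 √(0.15 × 0.85 + 0.23 × 0.77/r)]² / 0.08²
= [1.960 × 0.4929 + 0.842 × 0.4648]² / 0.0064 ≈ 287.9, so 288.

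The total is 3 × 288 = 864, which matches: "The unbalanced design requires 864 participants to achieve 80% power". At 300 UC and 600 AR + IVR the power is 81.7%; at 450 per arm it would be 86.5%. The article states no sample size, power or error rate for Aim 2.

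**2. Timing.** The last call is due by day 49 + 4 = 53 after discharge. Taking six months as about 180 days, the 30-day window opens near day 150. Calls therefore end well before the outcome window. Counseling and medication collection continues about six months beyond the outcome.

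**3. Trend test with no dose effect.** Taken from the article: 2 × 300 = 600 AR + IVR participants, 23% abstinent, the call days, the score components and the score χ² test. Assumed, because the article does not give them:

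- Relapse times among non-abstainers are exponential with mean 45 days, and draws beyond day 150 are replaced by uniform ones on days 0 to 150. Nobody quits again after relapse.
- A call is taken with probability 0.6 while abstinent and 0.6m after relapse.
- Program enrollment and medication start each have probability 0.3, unrelated to prognosis.
- Completion, judged at day 60, has probability 0.5 if abstinent and 0.5m if relapsed.

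The score is the sum (0 to 8). The statistic is z = Σy(d − d̄) / √[ȳ(1 − ȳ)Σ(d − d̄)²], rejecting if |z| > 1.96. There were 3,000 replicates per row, so the simulation error at 5% is √(0.05 × 0.95/3000) ≈ 0.4 percentage points. Odds ratios (OR) are one-step approximations from the score statistic, and the median is shown.

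| m (use after relapse ÷ while abstinent) | Full score: rejects | OR per level | Calls only: rejects | OR per call |
|---|---|---|---|---|
| 1.0 | 5.1% | 1.00 | 5.1% | 1.00 |
| 0.9 | 11.8% | 1.06 | 16.3% | 1.10 |
| 0.75 | 53.5% | 1.15 | 63.6% | 1.25 |
| 0.5 | 98.4% | 1.32 | 99.6% | 1.52 |
| 1.25 | 52.5% | 0.87 | 67.0% | 0.79 |
| 1.5 | 97.8% | 0.78 | not run | not run |

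At m = 0.75 and below every rejection is positive. At 1.25 and above every one is negative.

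**4. A different relapse curve.** Calls only, 400,000 patients, 20% abstinent, Weibull relapse with shape 0.5, call-taking 70% while abstinent. After-relapse call-taking of 60%, 50% or 40% gives an OR per call of 1.26, 1.56 or 1.88. At 80% the OR is 0.76.

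**5. Use between months 6 and 12 counted toward the six-month outcome.** Suppose the score adds one late-uptake item (20% in abstainers) to the two bedside items. If six-month smokers take it up twice as often as abstainers, the test rejects 72.4% of the time, always negative (OR 0.74). If half as often, it rejects 28.5%, always positive (OR 1.20).

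**6. Dose fixed before relapse is possible.** With dose set at discharge and unrelated to prognosis, the test rejects 5.2% of the time (OR 0.99). The day-53 landmark proposed under the fix was not simulated. In this model, though, everyone not yet relapsed by then had the same call probability throughout, so their earlier dose carries no information about later relapse.

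**The case against.** The best defense is that Aim 2 is secondary, the article condenses a fuller plan, and an exact dose window per outcome is often left to the analysis plan. That has force for the window taken alone. It does not cover what the article does fix: a score built largely from post-discharge use, tested for what the aim calls a dose effect.

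Several stronger readings are tempting, and the article does not support them:

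- *Aim 2 would show a dose effect even if none exists.* This requires relapsed patients to use less service, which the article never says. The IVR calls ask about smoking, encourage enrollment and offer a coach callback, so relapsed patients may use more. At m = 1 the error rate is nominal.
- *The dose runs past the outcome.* This is untrue for IVR calls. For counseling and medications it is the plain reading of *Intervention dose*, but it is not an explicit scoring rule, and for the twelve-month outcome the collection period does not overrun.
- *The score will be tuned to outcomes.* The text leaves inputs open to study data. It does not say outcome data will guide the choice.
- *2:1 allocation exists only for Aim 2.* A second reason is given.

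It is also fair that the adjusted Aim 1 model offers site, amount smoked, time to first cigarette and readiness. These are baseline factors and cannot remove dependence of dose on relapse after discharge. The same covariate list includes programs and medications used, which are parts of the dose. Finally, the portion of the pooled score that re-codes arm is randomized, but the pooled trend does not separate it from the rest.

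**Conclusion.** The point holds in a limited form. As written, the Aim 2 trend could be spurious in either direction, because dose accrues while abstinence is being kept or lost and no cut-off is stated for the six-month outcome. A modest dependence is enough: a ratio of 0.9 roughly doubles the false-positive rate (11.8% against 5%), and 0.75 or 1.25 raises it above 50%, with opposite signs. These sizes rest on assumed relapse times, uptake rates and use ratios. The article supplies only the sample size, the abstinence rate, the call days and the score components, so the actual bias cannot be stated. The reproduced sample size of 864 and the randomized intention-to-treat comparison are untouched. The analysis should be changed, but it does not threaten the trial's main conclusion.

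**What to change.** 1. Fix the score, its inputs and its levels before outcome data are seen, and drop the open-ended provision for further inputs.
2. For each outcome, count only use dated before a prespecified landmark that precedes the 30-day abstinence window, for example the close of the IVR call window at about day 53. Run the main dose analysis in AR + IVR participants not yet relapsed at that point, using the relapse timing collected under *Additional tobacco measures*. Adjust for site and for baseline dependence, readiness and confidence, but not for programs or medications used. Smoking status at the previous IVR call is not a substitute, because it is missing for patients who did not answer and for all of UC.
3. As a sensitivity analysis in AR + IVR only, define dose by what was accepted at the bedside (referral accepted, discharge medication ordered), which *Intervention fidelity* already documents. State that this leaves confounding by motivation.
4. Report full-period use and the pooled UC plus AR + IVR score as non-causal associations.

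Cost: analysis wording, with no new assessments. The landmark analysis has fewer participants and dose levels and less precision. It asks a narrower question, whether earlier use predicts staying abstinent from the landmark on, so an effect of dose on very early relapse is missed. It relies on recalled relapse dates, so a rule is needed for participants lost before they could give one.

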#### *IVR follow-up calls*

After discharge, AR + IVR recipients receive four IVR follow-up calls, at days 4, 14, 28, and 49 using Eliza Corporation’s IVR system [19]. The call receipt window will be +4 days for the initial call, and ±4 days for each subsequent call. Participants are prompted for information on current smoking status, cessation program enrollment status, and assessment of cessation medication use. Patients also receive brief, tailored, supportive messages to help them stay off cigarettes. These messages include encouragement to enroll in cessation programs, use cessation medications, or to speak to their doctor to determine the best course of treatment. IVR alerts are generated when a patient indicates that he/she would like to speak to an OTQL quit coach or KP health coach during the call. Study staff members facilitate a callback from the respective coach.

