#### *Specific Aim 1: estimate self-reported thirty-day abstinence at six and twelve months for patients assigned to receive inpatient AR + IVR compared to usual care*

Based on KPNW and OHSU member data and meta-analyses of effectiveness of hospital cessation programs with ≥1 month postdischarge follow-up, we expect about 15% of usual care patients and 23% of AR + IVR participants will be abstinent six months following discharge. The primary analysis assumes that nonrespondents are smokers.

The treatment effect on the primary outcome (and other binary outcomes) will be evaluated using logistic regression, logit[Y_ik_] = β_0_ + β_1_X_k_ + e _ik_ (Model 1), where Y_ik_ is the binary indicator of the observed binary smoking status for the i^th^ patient (i = 1,. . .,n_k_) within the k^th^ treatment condition (k = 1,2), X_k_ is the fixed effect of the k^th^ condition, that is, intervention or control, and β_0_, β_1_ are parameters to be estimated. Any difference between the predicted and observed values is left to the residual error (e _ik_) in this model. Multiple regression methods available in SAS PROC Logistic [33] will be used to estimate the parameters of this generalized linear model. The intervention fixed effect will be tested using the score *χ*^2^ test.

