## Discussion

Effective and cost-effective approaches to bridging inpatient and outpatient tobacco dependence treatment can be an important part of health system efforts to improve patient health and reduce future health-care costs. This study provides estimates of the health impacts, and economic impacts, of a practical approach to help smokers remain abstinent after hospital discharge. Our intervention protocol, providing brief inpatient cessation counseling, assisted referral to effective outpatient counseling and medications, and IVR follow-up over a seven-week period, is in line with the findings from a recent Cochrane meta-analysis showing that smokers with four or more weeks of cessation support after discharge were 1.65 (CI 1.44–1.90) times more likely to quit successfully after a year compared to those without support [3]. We expect to see a similar relationship between the AR + IVR and UC groups, but also expect a dose–response for participants based on the number of cessation services used (counseling sessions and medication days). Our 2:1 randomization strategy will allow us to evaluate the relationship between intervention dose and outcome.

The setting for this study provides an opportunity to compare study outcomes in two different health systems, a large comprehensive managed care organization and a large academic hospital. Since KPNW is a closed system, we expect the integration of inpatient and outpatient care to be more efficient there because of the ease of access to patient medical records and streamlined communications between inpatient medical staff, pharmacy staff, and outpatient care providers. Determination of plan benefit levels (for example, copays, medication availability) is also readily available. OHSU has a diverse patient population. Linking inpatient and outpatient care will be more complicated for OHSU participants since many patients do not have a regular health-care provider or are uninsured and receive outpatient care from providers or clinics outside of the OHSU system. Informing these providers about their patients’ cessation attempts will be more difficult. Also, access to services may vary based on differences in insurance coverage. We will evaluate whether these system differences affect treatment outcomes.

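### The pooled Aim 2 dose analysis, as plainly read, has no randomized-arm term and scores IVR calls that usual care cannot receive, so an arm difference can appear as a dose-response

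*Protocol article*

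**What the plan says.** Under Specific Aim 1 of the protocol article, the only systematic term in Model 1 is the randomized condition: "X_k_ is the fixed effect of the k^th^ condition, that is, intervention or control". Model 2 adds site, covariates and interactions, but treatment still enters only through X, and arm is not in the list under Covariates and effect modifiers.

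Specific Aim 2 builds on this: "We test the hypothesis in two ways using the model developed for Specific Aim 1". The first way is confined to AR + IVR recipients and will "redefine X as a multilevel ordinal variable representing intervention dose". The score combines "cessation service program enrollment and completion, cessation medications, and number of IVR follow-up calls received". The second way is the pooled one: "we will rerun the analysis including control group participants with a dose score using the same method". Trend tests and a threshold assessment are planned for each analysis.

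On the calls themselves, the intervention section says: "After discharge, AR + IVR recipients receive four IVR follow-up calls". The Study measures section confines them to the AR + IVR arm. UC patients may find counseling and medication for themselves, but the Study interventions section puts past use of such services after discharge below 1%.

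**The concern.** If X becomes dose and nothing puts the arm back, the pooled model has no place for a treatment difference except the dose coefficient. One component of the score is zero for every UC patient by design. The others are likely to be lower in UC, because staff help only AR + IVR patients to enroll and initiate discharge medication orders only for them. UC therefore sits at the bottom of the scale, and a UC patient who completes counseling and uses medication still scores below an AR + IVR patient with the same service use who took the calls.

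The bias does not need quitting to drive service use. It arises even when dose is unrelated to abstinence within each arm.

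The AR + IVR arm also includes things that the listed score does not count, such as notes to the primary source of care. An effect of those would be read as an effect of amount received. The stake is a stated specific aim and one of the reasons given for 2:1 allocation: the pooled tests cannot separate more services giving more quitting from assignment to AR + IVR giving more quitting.

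**Working it through.** **The plan's own figure.** Aim 2 states no figure, so the check starts from the primary sample size: 15% v 23%, 2:1, two-sided 5%, 80% power, no continuity correction (Power section). Average rate: (0.15 + 2 × 0.23)/3 = 0.2033.

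n(UC) = [1.96 × √(1.5 × 0.2033 × 0.7967) + 0.8416 × √(0.15 × 0.85 + 0.23 × 0.77/2)]² / 0.08² = (0.966 + 0.391)² / 0.0064 ≈ 288.

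Total 3 × 288 = 864, as the protocol states. With 300 UC and 600 AR + IVR, power is 81.7%.

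**What the pooled trend test picks up.** Suppose abstinence depends on arm only. Then corr(dose, abstinence) = corr(dose, arm) × corr(arm, abstinence), so the expected trend statistic is r × z(arm), where r is the correlation of the dose score with arm.

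- z(arm) = 0.08 / √(0.2033 × 0.7967 × (1/300 + 1/600)) = 0.08/0.02846 = 2.81.
- r = 0.49: expected z = 1.38; chance of exceeding 1.96 ≈ Φ(-0.58) = 0.28.
- r = 0.87: expected z = 2.45; chance ≈ Φ(0.49) = 0.69.

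**Simulation.** 300 UC at 15%, 600 AR + IVR at 23%, dose independent of abstinence within each arm. Score = enrollment + completion + medication + calls (0-4; 0 in UC). The test is the score test for trend, which equals the logistic score test, at two-sided 5%, with 3,000 runs per scenario. The protocol gives no uptake figures, so these are assumptions: per-call receipt 30-70%; enrollment and medication use each 20-50% in AR + IVR and 1-20% in UC; half of those enrolled complete.

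| Analysis | Trials showing a dose trend |
|---|---|
| Pooled, no arm term | 26-68% (45-62% at 50% call receipt) |
| Pooled, arm term kept | 3.9-6.2% |
| AR + IVR only | 3.9-6.2% |
| Pooled, calls dropped, no arm term | 4-38% |
| Pooled, calls dropped, arm term kept | 4.2-5.5% |
| Pooled, no arm term, 15% in both arms | 5.1% |

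Across these scenarios r runs from about 0.49 to 0.87, and the simulated extremes agree with the formula. The last row shows that the excess comes from the arm difference. The fourth row shows that dropping the calls alone is not enough.

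**Threshold test.** The expected share of zero-dose patients who are UC is 300(1-u₀)² / [300(1-u₀)² + 600(1-u₁)²(1-c)⁴], with c call receipt and u₁, u₀ the service use in AR + IVR and UC.

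- c = 0.3, u₁ = 0.2, u₀ = 0.2: 192/(192 + 92) = 68%.
- c = 0.7, u₁ = 0.5, u₀ = 0.01: 294/(294 + 1) = over 99%.

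A threshold placed at any dose versus none is thus mostly, and sometimes almost entirely, the arm comparison.

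**The case against.** The strongest reply is that the safeguard stands beside the problem. The dose analysis is run first in AR + IVR recipients alone, where arm cannot confound it, and a pooled trend with no trend there would alert a careful reader. This stands as far as it goes. A reader might infer that a false dose effect will be reported; the protocol does not support that. The pooled coefficient absorbs any arm difference, but whether the test is significant depends on uptake, and the first analysis offers a comparison. It does not correct the pooled result, which has its own trend and threshold tests and no stated limit on how they are read.

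Second, the protocol never says that the arm term is dropped. The redefinition of X is written for the single-arm analysis, where an arm term is impossible. That is right: the omission is the plain reading of rerunning the same method in Model 1 or Model 2, not an express statement.

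Third, zero calls is a true measurement for UC, and controls can serve as the low-dose anchor. But the randomized contrast is already tested in Aim 1, and repeating it under the name of dose adds no evidence of dose-response. Nor is the score simply arm under another name throughout: at r = 0.49 the shared variance is 0.49² = 24%, at 0.87 it is 76%.

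Fourth, a treatment effect wholly unrelated to anything received is an extreme case. Agreed. It is the null that a dose-response test is meant to hold at 5%, not a forecast.

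Finally, a reader might take the Discussion, which expects a dose-response "based on the number of cessation services used (counseling sessions and medication days", as a second, conflicting definition without IVR calls. It is a parenthesis about expectations; the operative definition is under Specific Aim 2.

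**Conclusion.** The point holds for the second, pooled Aim 2 analysis. On the plain reading it has no arm term and uses a score with a component closed to UC, so its trend and threshold tests mix the arm comparison with dose. At the protocol's planned rates and with no dose effect within arms, this gives a significant pooled trend in about 26-68% of trials, against about 5% with arm retained. The range rests on assumed call receipt, service use and score construction; the direction does not, so long as AR + IVR patients score higher on average and the arms differ in abstinence. The AR + IVR-only analysis, the primary outcome, the sample size and the randomized comparison are untouched. It is worth correcting because it bears on a stated aim, but it does not threaten the main result.

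**What to change.** For the pooled Aim 2 analysis, state that:

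- randomized arm stays in the model as a separate term beside dose;
- the pooled score uses only components open to both arms (program enrollment and completion, cessation medication), so that a given score means the same in each arm, and IVR calls count only in the AR + IVR-only analysis;
- dose-response and threshold conclusions rest on the arm-adjusted result, read beside the AR + IVR-only result, and both are labelled observational because service use is self-selected;
- any pooled trend shown without the arm term includes the arm comparison and is not separate evidence of dose-response.

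The arm term is the essential part.

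The change is one of wording, but the statistical cost is material. In simulations where dose truly caused the whole 15% v 23% difference (60% call receipt, service use 35% v 5%, calls kept in the score), the pooled test without arm detected it in about 96% of trials, the arm-adjusted test in about 61% and the AR + IVR-only test in about 58%. Under other uptake assumptions the arm-adjusted figure fell to about a third. The arm-adjusted analysis thus lies close to the AR + IVR-only one. The higher figure for the unadjusted test comes from borrowing the arm contrast that Aim 1 already tests.
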